#### Primary analysis

Descriptive statistics were calculated for all variables. Depending on the type of data were compared between the groups using either a *t* test (continuous) or chi-square (categorical).

The intervention group that receives postoperative instructions without any restriction on sleeping position will be declared non-inferior to the group that receives postoperative instructions with the advice to sleep in a supine position for the first 8 weeks postoperatively in case it can be demonstrated that the difference between these 2 groups does not exceed “a 3-fold difference in dislocation rate” in favor of the supine sleeping position group. This margin corresponds to the definition of clinically relevant difference in dislocation rate by Peak et al.

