### Main study parameters/endpoints

Primary outcome measure is the difference in dislocation rate, expressed as a percentage, within the first 8 weeks between the group that receives postoperative instructions with the advice to sleep in a supine position for the first 8 weeks postoperatively and the group that receives postoperative instructions without any restriction on sleeping position. The diagnosis of a dislocated hip will be confirmed by clinical examination and X-ray findings.

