### Sample size calculation

The maximum allowable difference in proportion in which there is still equality in the effect is not known in the literature. Previous studies suggested “a threefold difference in dislocation rate” to be a clinically relevant difference [4]. Since the literature is suggesting an average dislocation rate of 2.03 % [8] in the posterolateral surgical approach, a dislocation percentage between 2.03 and 6.09 % is considered to be “equal.” Hence, the planned sample size is *n* = 456 THA patients. (One-sided, *α* = 0.025, *β* = 0.80, missing data 20 %).

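### The non-inferiority margin is an absolute 4.06 percentage points in the sample size but is worded as a 3-fold difference in the decision rule, and the two can give opposite verdicts on the same data

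*Protocol article*

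**What the plan says.** Three sections of the protocol article bear on the margin.

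- **Sample size calculation.** It says "Previous studies suggested “a threefold difference in dislocation rate” to be a clinically relevant difference", takes 2.03% as the average rate for the posterolateral approach, and treats "a dislocation percentage between 2.03 and 6.09" % as equal. The total of 456 follows from this, with one-sided α = 0.025, 20% missing data, and a value of 0.80 printed as β that can only be the power.
- **Main study parameters/endpoints.** "Primary outcome measure is the difference in dislocation rate, expressed as a percentage, within the first 8 weeks".
- **Primary analysis.** The experimental arm is to be declared non-inferior on showing the following: "difference between these 2 groups does not exceed “a 3-fold difference in dislocation rate” in favor of the supine sleeping position group". This section prints neither 4.06 points nor 6.09%, and gives no reference rate and no confidence limit. A general sentence earlier in the section says that variables are compared by a t "test (continuous) or chi-square (categorical") test.

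**The concern.** A threefold difference and a 4.06-point difference are the same limit only when the concurrent control rate is 2.03%. The Background section itself cites dislocation rates from 0.5% to 10.6%, so the observed control rate may well lie elsewhere. Below 2.03% the absolute limit is the more lenient; above it, the ratio limit is.

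If the scale stays open until the data are seen, the primary conclusion can depend on which reading is picked afterwards. If the ratio is what is meant, the trial is far too small for the power it claims. An interval method could be left to an analysis plan. The scale of the margin cannot, because this document already words it in two ways.

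**Working it through.** **Inputs.** Control rate 2.03%, upper end of the band 6.09%, one-sided α = 0.025, power 80%, 20% missing and total 456, all from Sample size calculation. Assumptions: 1:1 allocation (not stated, but consistent with block sizes of 2, 4 and 6) and a true rate of 2.03% in both arms.

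**1. Reproduce 456.** Absolute margin: 6.09 − 2.03 = 4.06 points.

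n per arm = (1.96 + 0.8416)² × 2 × 0.0203 × 0.9797 / 0.0406² = 189.4, so 190. Total 380, and 380 × 1.20 = 456 exactly.

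Other versions do not reach 456:

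| Version | Evaluable total | × 1.20 |
|---|---|---|
| One-sided α = 0.05, 4.06 points | 300 | 360 |
| Superiority, 2.03% vs 6.09% | 740 | 888 |
| Ratio margin 3, log scale | 1,256 (628 per arm) | 1,508 |
| Ratio margin 3, score method | 1,344 (672 per arm) | 1,613 |

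The trial was therefore sized on the absolute scale. Because 20% was added rather than divided out, a 20% loss from 456 leaves 456 × 0.80 = 364.8, about 182 per arm and not 190.

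**2. Same data, both rules.** Upper limits of two-sided 95% intervals, 182 per arm:

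| Events, reduced vs usual | Risk difference (Wald; Newcombe) | Below 4.06? | Risk ratio (log) | Below 3? |
|---|---|---|---|---|
| 4 vs 4 | 3.0; 3.6 points | yes | 3.94 | no |
| 12 vs 10 | 6.0; 6.3 points | no | 2.71 | yes |

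The first row is close to what the plan expects: 182 × 0.0203 = 3.7 events per arm. Its split also holds for the ratio by the score method (3.60) and with all 228 per arm (2.4 or 2.9 points; ratio 3.95 or 3.61).

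**3. Power if the rule is a ratio.** SE of the log ratio = √(2 × 0.9797 / (n × 0.0203)); power = Φ(ln 3 / SE − 1.96).

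- n = 182: SE = 0.728, power 33%.
- n = 190: SE = 0.713, power 34%.
- n = 228: SE = 0.651, power 39%.

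Exact binomial enumeration of the log method at 182 gives 29% if a zero count in either arm is scored as failure, and 31% if 0.5 is added to zero counts. The score method gives 38%. The range at 182–190 is thus 29–34% by the log method and up to 38% by the score method.

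**4. Power if the rule is 4.06 points.** Exact enumeration:

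| Evaluable per arm | Wald | Newcombe | Miettinen-Nurminen |
|---|---|---|---|
| 182 | 78% | 66% | 62% |
| 190 | 81% | 68% | 66% |
| 228 | 86% | 78% | 75% |

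The planned 80% belongs to the simple normal formula at 190 per arm.

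**5. What 4.06 points allows at other control rates.** At 0.5%: (0.5 + 4.06) / 0.5 = 9.1-fold. At 1%: 5.06 / 1 = 5.1-fold. At 5%: 9.06 / 5 = 1.8-fold.

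**The case against.** The strongest reply is that the protocol has only one margin, named by its origin. Sample size calculation introduces it as a difference in proportions and converts threefold into a fixed band at 2.03%. The primary outcome is a difference in percentages. The decision rule also speaks of a difference between groups and puts 3-fold in quotation marks, as a label taken from a cited study. On that reading 4.06 points was meant throughout and simply never printed. This is a fair reading and stands as a possibility, so the documents do not establish that the sponsor adopted a ratio rule. They do leave the rule open: Primary analysis presents the 3-fold difference as the margin itself, and a reader applying that section alone would most naturally test a ratio.

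A reader might go further and infer that a non-significant chi-square result, or an observed ratio below 3, would be taken as non-inferiority. At true rates of 6.09% vs 2.03%, the chi-square test is non-significant in 47–49% of trials with 182–190 per arm, which would be a very high false-claim rate. The protocol states no such rule. The chi-square sentence follows a general one on descriptive statistics and is not tied to the primary outcome. The non-inferiority rule is a separate paragraph requiring demonstration, and a one-sided α of 0.025 is given elsewhere. That figure is therefore not a property of this plan.

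A further objection is that adopting the absolute rule is not free: the more reliable interval methods do not deliver 80% power, and at low control rates the rule tolerates more than a threefold increase. Both points stand and are carried into the fix.

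**Conclusion.** The concern holds as an inconsistency in the scale of the margin. The trial was sized on 4.06 points, the outcome is defined on that scale, and the decision rule is worded as 3-fold. The difference is large enough to reverse the primary conclusion at plausible counts, in either direction. If the ratio is meant, power is roughly 29–38% at 182–190 per arm instead of 80%, and about 628 evaluable patients per arm would be needed by the log method.

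These results rest on 1:1 allocation, a true rate of 2.03% in both arms, two-sided 95% limits, and 182 evaluable per arm after the plan's own 20% loss. The figure 4.06 is derived from 2.03% and 6.09%; it is not printed. The finding does not depend on how the chi-square sentence is read.

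**What to change.** In Primary analysis, state one rule on the scale used for sizing. Non-inferiority holds if the upper limit of the two-sided 95% confidence interval for the risk difference (reduced minus usual restrictions) is below 4.06 percentage points in both the ITT and PP populations. Name the interval method. Report the risk ratio and its interval alongside as descriptive, and say that the primary claim does not rest on a chi-square test of equality. The sponsor should confirm that 4.06 points is the margin intended.

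Restate the power for the chosen interval, using the figures in step 4 of the working.

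The change is one of wording and should be made before the outcome data are seen. Its costs should be disclosed:

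- With Newcombe or Miettinen-Nurminen limits the stated power falls below 80% even with no loss, so holding 80% would need more patients.
- The claim can no longer be phrased as less than 3-fold.
- At a low control rate 4.06 points allows more than a threefold increase, so the conclusion must be worded in percentage points.

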#### The secondary analysis

A repeated measure analysis of (co)variance (ANOVA; group and time) will be applied in order to investigate differences between the groups satisfaction, functional recovery (HOOS) and quality of life (EQ-5D) at 8 weeks, 6 months, 1 and 2 years postoperatively. In addition, correlation coefficients will be calculated between quality of sleep and functional recovery and quality of life. ANCOVA will be conducted dependent upon the analysis of differences in baseline characteristics between groups (e.g. preoperative values, age, radiographic analysis). Subgroup analysis will be directed towards identifying differences in functional recovery between patients with and without compliance and patients who were and were not satisfied.

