**Methods/Design:**

After providing informed consent a group of 456 patients with symptomatic coxarthrosis will be randomized to receive a THA either with care as usual, i.e. receiving postoperative restrictions including the advice to sleep in a supine position for the first 8 weeks postoperatively, or reduced restrictions with no recommendations regarding the position during sleeping. Primary outcome measure will be the percentage of early dislocations within the first 8 weeks after THA. Secondary outcome measures will be patient satisfaction, time to functional recovery, quality of sleep and patient’s self-reported compliance with postoperative instructions.

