**Discussion:**

To our knowledge this will be the first randomized controlled trial that compares a reduced restriction protocol with a restricted protocol following THA using a posterolateral surgical approach. Our hypothesis is that a reduced restriction protocol following THA with use of a posterolateral surgical approach has no influence on the early dislocation rate compared to a restricted protocol. Instead, embracing a reduced restriction protocol might even contribute to a higher quality of sleep, thereby facilitating a faster uptake and return to daily functions in patients after THA.

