### Secondary study parameters/endpoints

Secondary outcome measures are patient’s compliance with postoperative instructions, the influence of sleeping position restrictions on quality of sleep [18], the influence of sleeping position restrictions on patient satisfaction (anchor questions rating the degree of perceived quality of sleep and burden of the restrictions prescribed, the Client Satisfaction Questionnaire) and the effects of the advice to sleep in a supine position for the first 8 weeks on functional recovery.

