### Study procedures

After inclusion and prior to surgery, subject patients will complete the baseline questionnaire at the outpatient clinic during the intake by the nurse practitioner. The physiotherapist will mobilize patients on the day of the operation or the first postoperative day. During this mobilization patients are instructed how turn in bed and how to prevent more than 90 degrees of hip flexion and 45 degrees of rotation. The only difference in instruction between the two study arms is the sleeping position. When discharged to home or nursing home, patients receive a booklet describing the instructions relevant to the study arm they are assigned to. This booklet serves as an enchiridion for partners, physiotherapists, and other persons involved in the care of the patient. In addition, patients are handed a standardized diary booklet in which they are asked to document their sleeping position, exercise activities, experience of pain and any further comments they may want to convey. Patient will visit the outpatient clinic preoperatively and then at 8 postoperative weeks. Routine physical examination will be performed by the orthopedic surgeon. All scores and measurements will be recorded by the nurse practitioner who will also collect the diary booklet from the patients. Preoperative functional assessment will be done by pain severity (Visual Analogue Scale: range 0–10), hip function (Hip Disability and Osteoarthritis Outcome Score) and quality of life (EQ-5D). At 8 weeks follow-up the same functional assessment will be recorded by the nurse practitioner. This visit is combined with the regular postoperative control by the orthopedic surgeon. At 6, 12 and 24 months there will be follow-up questionnaires by Email, paper or telephone depending upon the availability of the patients’ Email addresses. The primary outcome: dislocations within the first 8 weeks, will be recorded in the patient’s file when visiting the emergency department.

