Another interestingly aspect of the current study compared to the existing literature is that fact that it incorporates an analysis of the patient self-reported compliance to postoperative restrictions. Our study plans to assess patient compliance to the sleeping position instructions in relation to their preferred sleeping position.

In summary, the aim of this RCT is to show that a reduced restriction protocol following THA with use of a posterolateral surgical approach has no influence on the early dislocation rate. By omitting the postoperative sleeping restriction patients might have a better quality of sleep, higher patient satisfaction and a faster functional recovery. To our knowledge this will be the first RCT that investigates use of a reduced restriction protocol following THA with use of a posterolateral surgical approach.

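### Quality of sleep is a secondary outcome defined as an effect of the restriction, but the secondary analysis leaves it out of the between-arm model and gives it only correlations

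*Protocol article*

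**What the plan says.** In the protocol article, the section on secondary study parameters/endpoints includes "the influence of sleeping position restrictions on quality of sleep" among the secondary outcomes. The abstract also lists it: "Secondary outcome measures will be patient satisfaction, time to functional recovery, quality of sleep". The abstract's discussion presents sleep as a route to recovery ("embracing a reduced restriction protocol might even contribute to a higher quality of sleep, thereby facilitating a faster uptake"), and the main discussion expects that without the restriction "patients might have a better quality of sleep, higher patient satisfaction and a faster functional recovery".

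The secondary analysis applies a repeated-measures model by group and time to "differences between the groups satisfaction, functional recovery (HOOS) and quality of life (EQ-5D) at 8 weeks, 6 months, 1 and 2 years". Sleep is not in that list. The next sentence adds that "correlation coefficients will be calculated between quality of sleep and functional recovery and quality of life". ANCOVA is then foreseen, depending on what the comparison of baseline characteristics shows.

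Two other places bear on the point. Under the primary analysis, a sentence without a grammatical subject says that data are "compared between the groups using either a *t* test (continuous) or chi-square (categorical"). Under study procedures, the listed preoperative measures begin "Preoperative functional assessment will be done by pain severity" and continue with HOOS and EQ-5D; that set is repeated at 8 weeks. The same section mentions a baseline questionnaire without itemising it.

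**The concern.** The endpoint section asks a between-arm question: does lifting the restriction change sleep? The secondary analysis answers another one: do patients who sleep better also have better function and quality of life? Such an association can be strong when the arms sleep equally well, and weak when they differ. It therefore carries no estimate of the arm effect. If the correlations were computed over both arms together, any arm difference would also be mixed into the association. The article does not say whether they are pooled or within arm.

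The stake is interpretive. Sleeping position is the only instruction that differs between the arms, and sleep is the benefit most directly linked to it. If non-inferiority on dislocation is shown, readers will want an estimate of what patients gain. As written, two other expected benefits, satisfaction and functional recovery, have a named between-arm model and sleep does not. The choice of test, time point and covariates for sleep would then be open to decision after the data are seen.

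**Working it through.** **1. Outcome against analysis**

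| Outcome | Named as a secondary outcome | In the group-by-time model | Other analysis named |
|---|---|---|---|
| Satisfaction | yes | yes | subgroup factor |
| Functional recovery (HOOS) | yes | yes | correlation with sleep; subgroup outcome |
| Quality of sleep | yes, worded as an effect of the restriction | no | correlation with function and quality of life |

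Quality of life (EQ-5D) is in the model too, although it is not in the list of secondary outcomes. Sleep is in that list and is missing from the model.

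**2. The plan's own sample size**

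Inputs from the sample size section: control rate 0.0203; margin 0.0609 − 0.0203 = 0.0406; one-sided alpha 0.025; power 0.80 (printed as β); 20% missing.

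n per arm = (1.96 + 0.84)² × 2 × 0.0203 × 0.9797 / 0.0406² ≈ 190 after rounding up, so 380 in total. 380 × 1.20 = 456, which matches the plan. Nothing in this point changes that figure.

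**3. What a between-arm sleep comparison could detect**

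The article gives no SD or expected effect for sleep, so differences are in SD units (two-sided alpha 0.05, 80% power). Evaluable patients: 456 × 0.80 / 2 = 182.4, taken as 182 per arm.

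Without a baseline score: 2.80 × √(2/182) = 0.29 SD. With the 190 per arm of step 2 it is also 0.29 SD.

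Adjusting for a baseline score with correlation ρ multiplies this by √(1 − ρ²). The equivalent sample size factor is 1/(1 − ρ²). The values of ρ are assumptions.

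| ρ (assumed) | Detectable difference, 182 per arm | Equivalent gain in patients | Power at 0.25 SD, 190 per arm |
|---|---|---|---|
| no baseline score | 0.29 SD | – | 0.68 |
| 0.3 | 0.28 SD | 10% | 0.72 |
| 0.5 | 0.25 SD | 33% | 0.80 |
| 0.7 | 0.21 SD | 96% | 0.93 |

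So a between-arm test is feasible with the planned patients. A baseline score adds little if ρ is near 0.3 and a good deal if it is near 0.7.

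**The case against.** The strongest reply is that sleep is not left without any comparison. The sentence on t tests and chi-square tests follows one about all variables, and a t test cannot apply to a binary dislocation outcome, so it reads as general. In addition, an anchor question on perceived sleep quality belongs to the satisfaction outcome, which is in the group-by-time model. The ANCOVA sentence is not limited to the three named outcomes. The correlations are introduced as an addition, not as the test of the arm effect.

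Much of this stands, and it rules out saying that sleep cannot be tested between arms. It does not remove the mismatch. The general sentence names no outcome or time point and provides no adjustment. ANCOVA is conditional on observed baseline differences. The anchor item is part of satisfaction, whereas the endpoint section lists quality of sleep separately, with its own reference.

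A reader might also infer that sleep is not measured at baseline. The article does not show this. The preoperative list is introduced as a functional assessment and is not an inventory of the baseline questionnaire. It also omits preferred sleeping position, which must be known before stratified randomisation. A condensed article may leave questionnaire contents to the full protocol.

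**Conclusion.** The point holds as a mismatch between a stated secondary outcome and its analysis: no dedicated between-arm analysis of sleep is specified, and the one analysis named for sleep does not estimate the arm effect. It should be corrected. It does not touch the primary endpoint or the sample size.

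Three stronger readings are not supported. The first is that the trial cannot show a sleep benefit: a randomised comparison at 8 weeks is unbiased without a baseline score and would detect about 0.29 SD. The second is that the lack of a baseline score invalidates the comparison: it would cost precision only, between 0.29 SD and 0.28, 0.25 or 0.21 SD under assumed correlations of 0.3, 0.5 or 0.7. The third is that the case for lifting the restriction rests on sleep alone: the main discussion puts sleep beside satisfaction and functional recovery.

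The detectable differences assume 20% missing data, equal arms and an approximately continuous sleep score.

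**What to change.** In the secondary analysis:

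- Add quality of sleep at 8 weeks, the end of the restricted period, as a between-arm outcome. Use ANCOVA on arm, operating surgeon and preferred sleeping position, plus the baseline sleep score where it is collected. Report the adjusted difference with its confidence interval.
- Specify this adjustment in advance, not depending on observed baseline differences.
- Compute the correlations of sleep with function and quality of life within arm, and label them descriptive.

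Confirm whether the baseline questionnaire already contains the sleep scale; if it does not, add it.

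The cost is one model line and at most one short scale in a questionnaire that patients already complete. Recruitment is under way, so if the scale has to be added, patients already enrolled will lack a baseline value; they still contribute to the 8-week comparison if the analysis allows for the missing covariate. The planned 456 patients stay as they are.

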## Methods/Design

### Study design

The study design is a single***-***center, parallel-group, stratified, randomized trial with a planned duration of 3 years in which 456 primary THA patients will be allocated to either a care-as-usual group receiving postoperative restrictions including the advice to sleep in a supine position for the first 8 weeks postoperatively or an experimental group, receiving postoperative instructions without restrictions on sleeping position after THA surgery. The experimental group does not use a pillow between the legs in any sleeping position and the care-as-usual group, that is only allowed to sleep in a supine position, is advised to use a pillow between the legs while doing so.

A non-inferiority design was chosen as a standard approach to assess similarity of results of the experimental as opposed to the care-as-usual treatment. In order to avoid an imbalance in treatment assignments and to reduce the opportunity for bias and confounders, a stratified blocked randomization technique will be applied with random sequences of varying block sizes (varying from *n* = 2, *n* = 4 or *n* = 6). Among the stratification factors are operating surgeon and the preferred self-reported sleeping position (supine, prone, on the side, combination/no clear preference) of the patient. Measurements will be taken at baseline (preoperatively), 8 weeks (at regular polyclinic visit) 6, 12 and 24 months after surgery (postoperatively).

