### Setting

Written informed consent, from patients who meet the inclusion criteria for participation in the trial, having verified that the candidate fully understands what is involved, will be obtained by the research nurse.

Patients will be recruited by the Center for Orthopedic Surgery OCON, Hengelo, The Netherlands. All THAs will be performed by one of OCON’s four orthopedic surgeons specialized in hip surgery and with at least 5 years’ experience in THA. Time, duration and type of anesthesia will be recorded in our patient database. The surgical approach is standard posterolateral with use of a capsular repair. The soft-tissue tension is optimized through neck-length adjustments until an axial force with the leg in extension produces 1 to 2 mm of soft-tissue laxity for male patients and 2 to 3 mm of soft-tissue laxity for female patients.

During trial reduction, stability of the hip is tested in full flexion; 90 degrees of flexion and 45 degrees of internal rotation; full extension; 0 degrees of extension and 45 degrees of external rotation; and with and without knee flexion (up to 90 degrees). Such stability testing is routine in our practice and was not modified for the present study. The implants that will be used are: Exceed ABT Ringloc-XShell, Biomet Orthopedics, E-Poly Hi-Wall Liner Biomet Orthopedics, Modular Taperloc complete femoral stem Biomet Orthopedics, Biolox Delta Modular Ceramic Head 32 mm (Dordrecht, The Netherlands). The postoperative protocol is full weight bearing to tolerance from day 1.

The first radiologic assessment, to control prosthetic positioning occurs on the day of the operation, with an anteroposterior (AP) and lateral view of the hip. The second radiographic assessment is at 8 weeks postoperative with an AP pelvic view and a lateral view of the hip. Implant position including cup inclination angle, acetabular component anteversion, hip offset, and leg length will be measured on the 8 weeks postoperative AP pelvic view. The target zones for anteversion and inclination are defined as 10–30 degrees and 30–50 degrees, respectively.

The local Medical Ethical Committee approves the study design, procedures, protocols and informed consent. The trial is registered at ClinicalTrials.gov NCT02107248.

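### Adjustment of the secondary outcomes depends on chance baseline differences, so the preoperative HOOS and EQ-5D scores would usually go unused as covariates and the model is not fixed in advance

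*Protocol article*

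**What the plan says.** The section on the secondary analysis (under Statistics) sets the main model: "A repeated measure analysis of (co)variance (ANOVA; group and time) will be applied" to satisfaction, HOOS and EQ-5D "at 8 weeks, 6 months, 1 and 2 years postoperatively". It then states the rule for covariates: "ANCOVA will be conducted dependent upon the analysis of differences in baseline characteristics between groups", with the examples "e.g. preoperative values, age, radiographic analysis". The same section plans subgroup analyses of functional recovery that compare "patients with and without compliance and patients who were and were not satisfied".

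Three other sections bear on this:

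- Study procedures: pain (VAS), HOOS and EQ-5D are recorded before surgery and again at 8 weeks.
- Study design: "Among the stratification factors are operating surgeon and the preferred self-reported sleeping position" of the patient.
- Setting: films are taken on the day of operation and at 8 weeks, and cup position, offset and leg length "will be measured on the 8 weeks postoperative AP pelvic view".

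**The concern.** In a properly randomised trial a baseline difference between arms is chance. Whether a covariate is worth including depends on how strongly it predicts the outcome. A strong predictor that happens to be balanced still removes residual variance, and the rule would leave it out. The preoperative score of the same instrument is the obvious case.

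The rule also leaves the model open. Which covariates enter depends on the observed data and on an illustrative list, so two analysts following the text could report different estimates.

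Two neighbouring statements add to this. Radiographic analysis is offered as a baseline characteristic, although the measurements are postoperative. And patients are to be grouped by compliance and satisfaction, both of which arise after randomisation and are themselves listed as secondary outcomes.

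What is at stake is the benefit side of the trial. The Discussion presents better sleep, satisfaction and functional recovery as the expected gains from lifting the sleeping restriction. The HOOS and EQ-5D comparisons should be as precise as the collected data allow.

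**Working it through.** **Inputs from the article.** The adjustment rule, example covariates, model and time points (secondary analysis); preoperative HOOS and EQ-5D (Study procedures); stratification factors (Study design); timing of films (Setting); 456 patients and 20% missing data (Sample size calculation).

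**Assumptions, not in the article.** Baseline-outcome correlation ρ of 0.3 to 0.6 (0.3, 0.5 and 0.7 in the simulation); one follow-up time; a two-sided 5% test as the trigger; a true effect of 0.25 SD for power.

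**1. The plan's own figure.** No size or power is given for the secondary analysis. The primary figure reproduces: with rate 0.0203 in both arms and margin 0.0609 − 0.0203 = 0.0406, n per arm = (1.960 + 0.842)² × 2 × 0.0203 × 0.9797 / 0.0406² ≈ 189.4, so 190. Two arms give 380, and 380 × 1.2 = 456. This point does not rest on that figure. It only sets the simulated arm size: 456 × 0.8 / 2 ≈ 182.

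**2. How often the rule triggers.** A 5% test on a variable that is balanced in expectation triggers 1 time in 20 (4.7 to 5.7% in the simulation). Even if any one of three independent tests brought in all the covariates, the chance would be 1 − 0.95³ = 14%. The preoperative score would usually stay out.

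**3. Variance with and without the baseline score.** Adjusted variance relative to post-only is 1 − ρ²; the equivalent gain in patients is 1/(1 − ρ²) − 1.

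| ρ | 1 − ρ² | Variance cut | Equivalent extra patients |
|---|---|---|---|
| 0.3 | 0.91 | 9% | 10% |
| 0.5 | 0.75 | 25% | 33% |
| 0.6 | 0.64 | 36% | 56% |

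**4. The conditional rule itself.** Simulation, 182 per arm, 6,000 runs per setting: adjust only if the baseline test has p < 0.05, against always adjusting.

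| ρ | Variance, conditional / always | Power, always | Power, conditional | Type I error, conditional |
|---|---|---|---|---|
| 0.3 | 1.07–1.08 | 70% | 67% | 5.0% |
| 0.5 | 1.24 | 78% | 67% | 4.3% |
| 0.7 | 1.66–1.69 | 91% | 69% | 3.8% |

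The variance ratio is a little below 1/(1 − ρ²) because the few trials with the largest imbalance do get adjusted. Power hardly benefits: never adjusting gives 66 to 67%.

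**5. If baseline is a level of time.** The listed times are all postoperative. If the model were nevertheless read as an analysis of change, the ratio of ANCOVA variance to change-score variance is (1 − ρ²)/(2(1 − ρ)) = (1 + ρ)/2, that is 0.65, 0.75 and 0.80 at ρ = 0.3, 0.5 and 0.6. Always adjusting is more precise under this reading too.

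**6. Radiographs.** The abstract has patients randomised after consent, to receive the operation under one protocol or the other. Every film described is taken on the day of operation or later, and the measurements come from the 8-week view, when the restriction period ends. None of this is baseline information.

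**7. Stratification factors and subgroups.** Surgeon and preferred sleeping position appear neither in the stated model (group and time) nor among the example covariates, and a rule triggered by imbalance would seldom select factors that the randomisation balances. On the subgroups, compliance with the sleeping advice also means different things in the two arms: one is told to sleep supine, the other may choose.

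**The case against.** The best case for the plan runs as follows. The model is called an analysis of (co)variance, and preoperative values head the list of candidate covariates, so baseline scores are not discarded. The list is illustrative and the article is condensed, so a full analysis plan could name the stratification factors. The article speaks of an analysis of differences and gives no 5% test. Implant position is set at surgery, before any sleeping advice takes effect. The subgroup comparisons are between kinds of patient, with no arm effect claimed.

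Much of this stands, and it rules out several stronger readings that a reader might infer:

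- *The rule inflates false positives.* It does not: simulated type I error was 3.8 to 5.0%.
- *The baseline scores are thrown away.* The text makes their use conditional; it does not exclude them.
- *Standard errors are invalid without the stratification factors.* Leaving the factors out typically makes standard errors too large, which is conservative, and nothing in the article bars the factors from the model.
- *Adjusting for implant position would seriously bias the comparison.* Any bias is probably small, so the label is what needs correcting.
- *The precision gain extends to sleep and satisfaction.* No preoperative score is described for either.

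The objection does not rescue the rule. It is stated outright, and an analysis plan that follows it cannot also fix the covariates in advance.

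**Conclusion.** The point holds as a free improvement to the secondary analysis, not as a threat to the validity of the trial. The primary dislocation comparison is untouched.

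The 9 to 36% cut in variance rests on the assumed correlation and a single follow-up time; the plan has four times in a repeated-measures model, so the exact figure will differ. How often adjustment is omitted rests on the assumed 5% trigger. That always adjusting is the more precise choice for HOOS and EQ-5D does not depend on whether the model is read as post-only or as change from baseline.

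Confidence is high for the conditional rule and for the radiographic label, where the secondary analysis and Setting sections conflict. The stratification part is weaker: the article is silent on those terms and does not misstate them. It belongs in the same rewritten sentence because the present rule would tend to keep the factors out.

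**What to change.** Replace the conditional ANCOVA sentence with a rule along these lines:

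*The HOOS and EQ-5D models include the preoperative value of the outcome as a covariate. All secondary outcome models include the stratification factors used in the randomisation (operating surgeon and preferred sleeping position). These terms are included whatever the observed baseline balance, and baseline differences are not used to select covariates.*

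Then make two smaller edits:

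- Remove radiographic analysis from the examples of baseline characteristics. Keep any adjustment for implant position as an exploratory sensitivity analysis, and state which film it uses.
- Label the compliance and satisfaction subgroup analyses as descriptive, because both groupings are defined after randomisation.

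The cost is wording in the protocol or analysis plan, to be settled before outcomes are compared by arm. No new data, visits or patients are needed. With four surgeons and four sleeping-position categories entered as main effects, the stratification factors add 3 + 3 = 6 parameters, which is modest for a trial of 456.
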